### 2.6. Recruitment, Allocation, and Blinding

The patients will be recruited as they attend their usual consultations with the neurologist, where they will be proposed to take part on the study based on the fulfillment of the established eligibility criteria. Information about the project will be posted on the institutional website where the study will be carried out.

Concerning the allocation concealment procedures, an external researcher will conduct central randomization using computer-generated random numbers (www.randomizer.org), performing a simple randomization. The two lists, DN and placebo groups, comprising a total of 40 patients, will be sent by email to the physical therapist who will perform the intervention, with the randomized numbers assigned to each group. Those numbers will correspond to the recruitment order of each patient, and they will be assigned by the physical therapist in charge of the evaluation, who will remain unaware of the allocation sequence (blinded evaluation).

To ensure blinding, participants will be fitted with a mask so they will not be able to see the type of needle used. Additionally, care providers will not be allowed to access to the room where the intervention will take place, and data analysts will be blinded to participants’ allocation group. All patients will be informed of their group allocation after analyzing the study findings. If real DN shows to be superior to placebo DN, participants in the placebo group will be allowed to receive the real DN protocol.

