### 2.3. Procedure

The flowchart of the study process is shown in Figure 1 and Figure 2. At a first appointment, a neurologist will carry out a complete neurological evaluation of each patient to assess for eligibility. Data collection will be carried out at baseline (first visit) and between 6 and 8 days after the intervention protocol by a researcher (evaluator) who will be blinded to participants’ allocation group. The intervention in both groups will be performed by another senior physiotherapist, who is experienced in the use of DN.

The lead researcher (physical therapist) will get the signed informed consent forms, where the study details will be clearly explained, and the patients will be informed that his/her participation is voluntary so they can withdraw at any moment with no need to provide any specific reason.

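### Only the generation of the sequence is central: both allocation lists, keyed to recruitment order, go to the on-site treating physiotherapist, so concealment from enrolling staff is weakly protected

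*Protocol article*

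**What the plan says.** Section 2.6 gives the procedure in four steps, which it introduces as the means of allocation concealment.

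- Generation: "an external researcher will conduct central randomization using computer-generated random numbers (www.randomizer.org), performing a simple randomization".
- Custody: the two lists, one per group and 40 patients in all, "will be sent by email to the physical therapist who will perform the intervention, with the randomized numbers assigned to each group".
- Key: "Those numbers will correspond to the recruitment order of each patient".
- Numbering: "they will be assigned by the physical therapist in charge of the evaluation, who will remain unaware of the allocation sequence".

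The steps by which a patient enters the trial are described partly in the same section and partly in section 2.3. On recruitment: "The patients will be recruited as they attend their usual consultations with the neurologist". The neurologist also judges eligibility (section 2.3). On consent: "The lead researcher (physical therapist) will get the signed informed consent forms". Section 2.3 adds that the treatment in both groups is given by a senior physiotherapist who is a different person from the evaluator. Assessment and treatment take place in the same unit (sections 2.2 and 2.4).

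**The concern.** Allocation is concealed when the people who decide whether and when a patient enters cannot know the arm that the patient will receive. A central service achieves this by keeping the sequence and disclosing each assignment only after the patient is irrevocably in the trial. Here the external researcher generates the sequence and then passes the whole of it to a member of the site team, in a form that can be read directly against the running count of recruits.

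If that knowledge reached anyone who proposes the trial, judges eligibility, takes consent or sets the appointment, the choice or timing of entry could be steered, knowingly or not. The masking that the protocol plans for patients, evaluator and analysts acts after entry and cannot remove selection at entry. The analysis in section 2.8.2 compares groups with t-tests or Mann-Whitney tests and states no baseline adjustment that might lessen the effect of such selection.

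**Working it through.** The protocol states no figure on concealment, so there is none to reproduce. The check sets the stated roles beside the stated access to the sequence.

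| Role | Task at entry | Stated to receive the lists? | Stated to be unaware of the sequence? |
|---|---|---|---|
| External researcher | None stated | Generates them | Not applicable |
| Neurologist | Recruits, judges eligibility (2.3, 2.6) | No | No |
| Lead researcher, a physical therapist | Takes consent (2.3) | Not stated | No |
| Evaluator | Assigns numbers, measures outcomes (2.3, 2.6) | No | Yes (2.6) |
| Treating physiotherapist | None stated | Yes, both lists (2.6) | Not applicable |

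**1. What the list holder needs and what the list holder gets.** To give real or sham needling to patient number *k*, the therapist needs one assignment, that of patient *k*. Lists covering 40 numbers also disclose the 40 − *k* assignments still to come. At the first patient that is 40 − 1 = 39 assignments not needed for delivery; at the twentieth it is 40 − 20 = 20. With release one at a time it is 0 throughout.

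**2. How predictable the next arm is.** Under simple randomisation with equal probability (the ratio is assumed, since it is not stated), a person without the lists guesses the next arm correctly with probability 1/2. A person with the lists and the enrolment count knows it with probability 1, because the key is recruitment order.

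**3. Which roles are kept apart.** Section 2.3 separates the treating physiotherapist from the evaluator. No sentence separates the treating physiotherapist from the lead researcher who takes consent. The text neither says that they are one person nor that they are two.

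**4. When the lists are sent.** No date is given. That the lists are sent ahead of recruitment is an inference, though a strong one, because they cover all 40 recruitment numbers.

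**5. Does simple randomisation add to the point?** Inputs: N = 40 and d = 0.93 for the Modified Ashworth Scale (section 2.8.1). Assumed: a two-sided t-test at 0.05, since sidedness is not stated, and independent assignment with probability 1/2. The chance of exactly 20:20 is C(40,20)/2^40 = 12.5%; the chance of 25:15 or worse is 15.4%. Power from the noncentral t is 81.8% at 20:20 and 80.7% averaged over the binomial distribution of splits. The average cost is about 1 percentage point.

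**The case against.** The strongest reply is that concealment concerns those who select, enrol and number patients, and that the only stated recipient of the lists does none of these in the text. The treating therapist must learn each allocation in order to deliver it. The neurologist is not said to receive anything. The evaluator who assigns the numbers is expressly kept unaware. Nothing shows that the lead researcher and the treating physiotherapist are the same person, and a condensed article may well leave staffing detail to the full protocol.

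Much of this stands. It rules out the stronger reading that a reader might infer, namely that concealment does not exist or that the person enrolling patients holds the list. The text shows neither.

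It does not dispose of the point. The therapist needs the current patient's arm at session 1, not the arms of later patients. The assurance for the evaluator is labelled as blinded evaluation and does not extend to recruitment or consent. And the release of whole lists keyed to recruitment order is a procedure that the article states, not a detail that it leaves out.

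**Conclusion.** The point holds as a weakness in a stated procedure. Randomisation is central in generation only; custody of all 40 assignments passes to an on-site trial therapist, and the protection of concealment then depends on that person having no part in, and no influence on, recruitment and consent, which the article does not state. The conclusion rests on reading the lists as sent whole, which the text says, and before recruitment ends, which it implies.

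The size can be given only as exposure: up to 39 future assignments known to one person on site, against none under single release. It cannot be turned into a bias in outcome units. Section 2.8.2 analyses pre-post differences, so steering would have to act on expected change rather than on baseline level, and the documents give no basis for a figure.

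A reader might also infer that simple randomisation is a defect here. The documents do not support that. The method is valid and is the least predictable one, section 2.8.1 gives totals without arm sizes, and section 2.6 does not say how the two lists were formed; if they were fixed sets of 20 numbers, the binomial figures would not apply. At about 1 point of power on average, restricted randomisation is an optional preference, and blocking would not restore concealment while the list is exposed.

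**What to change.** - The external researcher keeps the sequence. After consent, baseline assessment and recording of the study leg, the evaluator registers the patient number, and the external researcher sends that one allocation to the treating physiotherapist at session 1. The leg is recorded first because section 2.4 selects it from the Modified Ashworth scores, and that choice should be settled before anyone on site knows the arm.
- The protocol states that whoever holds allocations takes no part in recruitment or consent, and that the neurologist and the lead researcher have no access to the sequence.

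The cost is one short message per patient, 40 in all, from a person who already has a role in the trial.

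The abstract puts the assignment of the forty patients in the past tense, while the rest of the article uses the future tense, so the status is unclear. If allocation is complete, the procedure can no longer be changed. The trial report should then say when the lists were sent, who saw them, and whether the list holder had any part in recruitment or consent. That costs a few sentences.

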### 2.7. Data Collection and Management

The data will be entered directly into the computer where the patient’s medical record is stored, which is placed in the facilities where the evaluation will be carried out. This process will guarantee the security of the data. For the exchange of data between researchers for further analysis, an Excel page will be sent, including only the identification number of each patient.

### 2.8. Statistical Methods

#### 2.8.1. Sample Size

The G*Power version 3.1 statistical software (Heinrich-Heine-Universität Düsseldorf) was used to estimate the sample size and statistical power. According to Salom-Moreno et al. [21] the between groups difference in pressure pain sensitivity, assessed with a pressure algometer, was 39.7 ± 79.92 kPa (effect size *d* = 0.49) in the anterior tibialis muscle of the affected side. Furthermore, since this previous study did not use a placebo group as a comparison group, the study of Ghannadi et al. [25] was considered to calculate the sample size according to the MAS, that showed a difference between groups of 0.75 ± 0.82 points (effect size *d* = 0.93). This would require a sample size of at least 38 participants. An alpha level of 0.05 was assumed to perform the analysis. In both cases, the calculated sample size had an 85% power to detect statistically significant and clinically meaningful changes in pressure pain sensitivity and spasticity. Therefore, we considered 40 patients to be an adequate sample size for the proposed study.

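### The 85% power claimed for pressure pain is about 33% (two-sided) for the between-group comparison with 40 patients; the spasticity figure depends on an unstated sidedness

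*Protocol article*

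**What the plan says.** Section 2.8.1 (Sample Size) of the protocol article uses two external results.

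- **Pressure pain:** the between-group difference in pressure pain sensitivity "was 39.7 ± 79.92 kPa (effect size *d* = 0.49").
- **Spasticity (MAS):** because the first source had no placebo arm, a second study is used, "that showed a difference between groups of 0.75 ± 0.82 points", with "effect size *d* = 0.93".

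The required number follows: "This would require a sample size of at least 38 participants". On error rates the section says only "An alpha level of 0.05 was assumed to perform the analysis". It then claims power for both outcomes, pressure pain and spasticity: "In both cases, the calculated sample size had an 85% power". From this it concludes that "we considered 40 patients to be an adequate sample size".

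Section 2.8.2 (Data Analysis) plans unpaired tests between groups (independent t-test or Mann–Whitney U), paired tests within groups, 95% confidence intervals, and alpha 0.05 throughout. Neither section says whether tests are one- or two-sided. Section 2.1 describes a placebo-controlled superiority trial.

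**The concern.** The two effect sizes differ by almost a factor of two (0.49 against 0.93). At fixed alpha and power, the required number scales with 1/d², so the smaller effect needs about (0.93/0.49)² = 3.6 times as many patients. One sample size of 38 to 40 cannot give the same 85% power for both between-group comparisons.

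The 85% figure is the stated reason for regarding 40 patients as adequate for both outcomes. If the trial finds no difference in pressure pain, a reader relying on it would take that as fairly strong evidence against an effect of the assumed size. With power near 33%, the trial would miss such an effect about two times in three.

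A smaller question concerns the MAS: whether 38 patients at 85% power can be reproduced, and under which test.

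**Working it through.** **Inputs.** From Section 2.8.1: pressure pain 39.7 and 79.92 kPa, printed d = 0.49; MAS 0.75 and 0.82 points, printed d = 0.93; alpha 0.05; power 85%; N = 38 required, 40 planned. Assumptions: equal arms (19 or 20 each; the allocation ratio is not stated) and no loss to follow-up (no figure is given).

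**Effect sizes.** d = difference / SD.
- Pressure pain: 39.7 / 79.92 = 0.497 (printed 0.49).
- MAS: 0.75 / 0.82 = 0.915 (printed 0.93). Allowing for rounding of the inputs, the ratio lies between 0.745/0.825 = 0.903 and 0.755/0.815 = 0.926.

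**Method.** Two independent groups of n each, t-test, noncentral t with noncentrality d·√(n/2) and 2n − 2 degrees of freedom. For example, with d = 0.49 and n = 20, the noncentrality is 0.49 × √10 = 1.55. The two-sided critical value on 38 degrees of freedom is 2.02, so the expected test statistic falls short of the threshold and power must be well below 50%.

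**Step 1: reproduce the plan's 38 (MAS, d = 0.93, 85% power).**

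| Test | One-sided 5% | Two-sided 5% |
|---|---|---|
| t-test | 17.34 per arm, N = 36 | 21.77 per arm, N = 44 |
| Mann–Whitney (asymptotic relative efficiency 0.955) | N = 38 | N = 46 |

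The figure is matched exactly by a one-sided Mann–Whitney test and to within two patients by a one-sided t-test. Neither two-sided test gives it.

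**Step 2: MAS power at 38 and 40 patients (t-test).**

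| d | Two-sided, N = 38 / 40 | One-sided, N = 38 / 40 |
|---|---|---|
| 0.93 | 79.7% / 81.8% | 87.8% / 89.3% |
| 0.915 | 78.3% / 80.5% | 86.9% / 88.4% |

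**Step 3: pressure-pain power, between groups (t-test).**

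| d | Two-sided, N = 38 / 40 | One-sided, N = 38 / 40 | N for 85%, two-sided / one-sided |
|---|---|---|---|
| 0.49 | 31.2% / 32.7% | 43.5% / 45.1% | 152 / 122 |
| 0.497 | 32.0% / 33.4% | 44.3% / 45.9% | 148 / 118 |

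No combination of sidedness and rounding comes near 85%.

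**Step 4: could another test explain 85% for pressure pain?** A two-sided paired or one-sample t-test with d = 0.49 gives 83.7% with 38 subjects and 85.6% with 40. This is a possible origin of the figure, though the article does not say so. It would describe change within a single group of 38 to 40 people. It is not a comparison of needling with sham in arms of about 20, and Section 2.8.1 presents the 39.7 kPa as a difference between groups.

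**The case against.** The best defence concerns the MAS. The article never states a two-sided test, and 38 patients can be reproduced with a one-sided one. Section 2.8.2 names the Mann–Whitney test for non-normal data, which is plausible for a coarse scale such as the MAS. Even if the tests are two-sided, power at 40 patients stays just above 80%. All of this stands. A reader might infer that the plan promises 85% two-sided power and misses it, or that the MAS sample size is an error; the text supports neither. The planned 95% intervals and usual convention point to two-sided testing but do not settle it.

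A reader might also infer from 0.75/0.82 that the effect size was miscalculated. The upper rounding limit, 0.926, itself rounds to 0.93, and the source study's unrounded values are not available here. The gap moves two-sided power by about 1.3 percentage points. The pain value of 0.49 looks like 0.497 truncated and matters even less.

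Finally, a condensed article may leave details such as sidedness to a fuller document. That is a fair answer to an omission. It does not answer the pressure-pain figure, which is stated outright and fails under either sidedness. Sidedness is worth raising only because the printed number of 38 depends on it.

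**Conclusion.** The statement that 38 to 40 patients give 85% power in both cases is wrong for pressure pain. From the article's own effect size, between-group power is about 31–33% two-sided or 44–46% one-sided, and 85% would need roughly three to four times the planned number (118/40 = 3.0 to 152/40 = 3.8).

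For the MAS the conclusion is conditional. The sample size implies a one-sided 5% test that the article does not declare. If the tests are two-sided, power with 40 patients is about 80–82%, which is 3 to 5 points below the stated 85%; if one-sided, it is about 88–89%.

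These figures assume equal arms, complete follow-up and a t-test. Simple randomization can leave the arms unequal, which would lower power slightly. It does not follow that the trial must be enlarged: the number of 38 comes from the MAS, and the defect lies in the power claimed for pressure pain.

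**What to change.** In Section 2.8.1:

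1. Remove the statement that both outcomes have 85% power.
2. Give pressure-pain power with 40 patients as about 33% two-sided (about 45% one-sided), so that a null result on this outcome is read accordingly.
3. State whether the tests are one- or two-sided, and give the matching MAS power for 40 patients: about 80–82% two-sided or 88–89% one-sided.
4. Name the test behind the figure of 38.
5. As a minor point, reconcile the printed MAS effect size of 0.93 with 0.75/0.82 = 0.91, or say that it comes from unrounded values.

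The cost is wording and a less favourable stated power. No added enrolment, new data or change to the planned tests is required.

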#### 2.8.2. Data Analysis

Statistical Analysis will be performed by PASW STATISTIC 18 for Windows. Descriptive statistics will be calculated to show a summarized overview of the data, including frequency counts for categorical variables and central tendency and dispersion measurements for continuous variables. Means, standard deviations (SD) and 95% confidence intervals (CI) will be calculated for continuous variables. The Kolmogorov-Smirnov test will be used to check the normality of the data. Baseline characteristics will be compared between groups to assess the adequacy of the randomization process and analyze the homogeneity of the sample. Independent t-test (normal distribution) or Mann–Whitney U test (non-normal distribution) for continuous data or chi-square tests of independence for categorical data will be used for this purpose. Furthermore, within groups (paired) and between groups (unpaired) pre-post intervention differences will be analyzed using the abovementioned statistical tests, considering the nature of each variable. For all the analyses, an a priori alpha level of 0.05 will be used.

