### 2.5. Outcomes

Clinical assessment of gait performance, spasticity level, electromyographic activity, pain, ROM, and QOL will be reported in the first and third visit (Figure 2). Several outcome measures will be collected to get a better understanding of the treatment effect and because of their extensive use in research on these topics. This will allow us to compare our results with those reported in previous studies. Following the guidelines of the International Classification of Functioning, Disability and Health [38], some of the outcomes will be devoted to investigate functional parameters, such as gait parameters and QOL. The outcome measures and the tools to assess them are detailed below:

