#### 2.5.1. Gait Performance

The GaitRite^®^ system will be used to measure several gait parameters (average gait speed, walking cadence, step length, stride length, step width, and percentage of support-oscillation) [39,40]. During the overground walking assessment, participants will walk at preferred speed along an 8.62 m walkway (the length of the tapestry). Data about gait parameters will be collected with motion sensors placed directly in the tapestry.

The two-minutes walking test (2MWT) [41] will be used to assess functional capacity. Given the difficulty that many patients with MS have to walk for 6 min, we propose the 2MWT in the present protocol. The 2MWT is valid in pwMS and provide an efficient and alternative to the 6MWT.

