#### 2.5.2. Spasticity

The Modified Ashworth scale (MAS) [42] will be used to assess the spasticity level over the RF and GM muscles. The reliability of the MAS has been demonstrated in LE muscles, e.g., knee extensors and plantar flexors. Thus, this scale is a valid tool for the present protocol. Even though the MAS only measures the passive component of spasticity, the electromyographic evaluation detailed below would provide some information on the spastic co-contraction phenomena during the execution of analytical movements.

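### Baseline significance tests cannot show that randomisation was adequate, and the between-group tests of change forgo a free adjustment for baseline

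*Protocol article*

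**What the plan says.** Section 2.8.2 gives the baseline comparison a stated purpose: "Baseline characteristics will be compared between groups to assess the adequacy of the randomization process and analyze the homogeneity of the sample". The tools named for it are "Independent t-test (normal distribution) or Mann–Whitney U test (non-normal distribution) for continuous data or chi-square tests of independence for categorical data". The threshold follows at the end of the same section: "For all the analyses, an a priori alpha level of 0.05 will be used".

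The same section then analyses pre-post differences within and between groups with those tests. For the between-group comparison this means an unadjusted two-sample test of change.

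Three other places matter:
- Section 2.6: allocation uses "computer-generated random numbers (www.randomizer.org), performing a simple randomization".
- Section 2.8.1: "we considered 40 patients to be an adequate sample size".
- Section 2.5: "Clinical assessment of gait performance, spasticity level, electromyographic activity, pain, ROM, and QOL will be reported in the first and third visit", so each outcome has a baseline value and a post-treatment value.

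The article does not list the baseline characteristics to be tested, says nothing about which pattern of p-values would count against the randomisation, and ties no later step to the result.

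**The concern.** The null hypothesis of a baseline test is that the arms differ only by chance. If the computer-generated sequence is followed, that null is true by design. A small p-value is then a chance event and a large one confirms nothing, so the first stated purpose, judging the randomisation, is not served.

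The second purpose, judging homogeneity, is not served either. In a trial of 40, an imbalance can be large enough to matter and still be non-significant.

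Two things are at stake. The report may describe a sound randomisation as doubtful, or declare comparable two groups that differ noticeably. And baseline information that is already collected would be spent on these tests and on subtraction, when as a covariate it would give a more precise treatment comparison that is protected against chance imbalance.

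**Working it through.** The article states no error rate for the baseline check, so there is no figure of its own to reproduce.

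**Inputs.** From the article: alpha 0.05 per test, 40 patients, simple randomisation. Assumed: two-sided tests and 20 per arm (simple randomisation does not guarantee an even split, and an uneven one lowers power).

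**1. Can the tests show comparability?** The standard error of a difference in means, in SD units, is √(2/20) = 0.316.
- Power of the two-sample t-test for a true 0.5 SD difference (noncentral t, 38 df): 34%.
- An observed difference is significant only above about 2.02 × 0.316 = 0.64 SD. An observed 0.5 SD imbalance gives t = 0.5/0.316 = 1.58 and would pass as homogeneous.
- Under perfect randomisation an imbalance above 0.5 SD on a given variable has probability P(|Z| > 1.58), about 11%.

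The 0.5 SD is a yardstick chosen here. The article defines no harmful imbalance.

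**2. How often would a sound randomisation give a significant result?** Per test: 5%. For at least one among k independent tests: 1 − 0.95^k.

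The article does not fix k. If all outcome variables are tested at baseline, sections 2.5.1 to 2.5.6 give this count:
- gait: 6 ("average gait speed, walking cadence, step length, stride length, step width, and percentage of support-oscillation") plus the two-minute walk, 7
- MAS, which "will be used to assess the spasticity level over the RF and GM muscles": 2
- sEMG: maximal contraction in 2 muscles, plus root mean square in 2 muscles × 2 walking situations, 6
- pressure pain threshold: 4 sites × 2 sides, 8
- ROM: at least 3
- quality of life: 1

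Total 7 + 2 + 6 + 8 + 3 + 1 = 27. If the phrase means mainly demographic and clinical descriptors, k could be 5 to 10.

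Chance of at least one p<0.05. The zero-correlation column uses the formula; the others come from simulated t-tests with 20 per arm and equal correlation among variables:

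| Variables | 0 | 0.3 | 0.5 | 0.7 |
|---|---|---|---|---|
| 5 | 23% | 21% | 19% | 15% |
| 10 | 40% | 36% | 30% | 21% |
| 27 | 75% | 64% | 49% | 34% |

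With 27 variables in domain blocks (correlation 0.5–0.8 within a domain, 0.1–0.3 between), the figure is 48% to 66%.

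**3. What does baseline adjustment add?** Let σ be the common pre and post SD and ρ the pre-post correlation. Neither is in the article; equal SDs and ρ = 0.5 to 0.8 are assumed.
- Variance of a change score: 2σ²(1 − ρ).
- Residual variance after adjustment for baseline: σ²(1 − ρ²).
- Ratio: (1 − ρ²)/[2(1 − ρ)] = (1 + ρ)/2.
- ρ = 0.5: ratio 0.75, a 25% cut; 40/0.75 ≈ 53.
- ρ = 0.8: ratio 0.90, a 10% cut; 40/0.90 ≈ 44.

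These ratios ignore the small cost of estimating one slope.

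Given a chance baseline imbalance δ, regression to the mean shifts the difference in change by (1 − ρ)δ in size. For δ = 0.5 SD that is 0.25 SD at ρ = 0.5 and 0.10 SD at ρ = 0.8. Adjustment removes this shift.

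**The case against.** The strongest reply is that nothing depends on these tests. No exclusion, covariate choice or stopping decision in the article follows from them, so the treatment comparison is the same whatever they show. This stands, and it limits the harm to what is said about the randomisation.

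A reader might infer that the plan contains a rule that condemns a sound randomisation about half the time or more. The article does not support that. It has no rule that any single p<0.05 means failure, and no list or count of variables. The higher percentages require both to be supplied, along with modest correlation. Strong correlation is plausible for step and stride length or for left and right pressure thresholds, and it brings the figure down.

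A reader might also infer that baseline is not used at all or that the treatment comparison is biased. Neither follows. Testing pre-post differences subtracts each patient's baseline, and under randomisation that comparison is unbiased. What remains is a loss of precision and a distortion conditional on a chance imbalance.

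Baseline tests might be defended as a screen for subverted allocation, where the null could be false. With 34% power against a systematic 0.5 SD difference, a clean result would give little reassurance.

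Finally, covariate adjustment is often left to a full analysis plan. Here, however, the article does not leave the method open: it names unadjusted two-sample tests for the between-group comparison.

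**Conclusion.** The point holds as a badly fixed analysis choice with limited consequences. Section 2.8.2 commits to tests that can establish neither the adequacy of randomisation nor comparability of the arms. The only false-alarm rate that the article itself fixes is 5% per test; the 15% to 75% range for at least one significant result rests on the assumed count and correlation in the table. Nothing here indicates that the randomisation is faulty.

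The lack of baseline adjustment is a separate matter of efficiency. The 10% to 25% variance reduction depends on the assumed correlation and equal SDs, but its direction does not: for any ρ below 1, (1 + ρ)/2 is below 1. In a trial of 40 that gain is worth having.

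**What to change.** In section 2.8.2:
- Delete the baseline significance tests and the statement that they assess randomisation.
- Tabulate baseline characteristics by arm descriptively (means and SDs, medians where suited, counts).
- Pre-specify that each between-group comparison adjusts for that outcome's own baseline value: ANCOVA for continuous outcomes and an ordinal model for the MAS. Apply this whatever the baseline table shows, so that the choice is not driven by observed imbalance.

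The cost is a change of analysis wording. It needs no new data, visits or patients, because every outcome is already measured before and after treatment.

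### Between-group effects are tested on unadjusted pre-post differences, by a test picked after a normality check, although every outcome domain has a baseline; baseline adjustment would usually be more efficient, by an amount that depends on the pre-post correlation.

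*Protocol article*

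**What the plan says.** Section 2.8.2 fixes the efficacy comparison: "between groups (unpaired) pre-post intervention differences will be analyzed using the abovementioned statistical tests". The tests it points back to are "Independent t-test (normal distribution) or Mann–Whitney U test (non-normal distribution) for continuous data", and chi-square tests for categorical data. The deciding check is given just before: "The Kolmogorov-Smirnov test will be used to check the normality of the data". The same tests are planned for comparing baseline characteristics between arms. The article contains no baseline-adjusted model.

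The baseline values will exist. Section 2.3 says "Data collection will be carried out at baseline (first visit) and between 6 and 8 days after the intervention protocol", and section 2.5 says that gait, spasticity, electromyography, pain, range of movement and quality of life "will be reported in the first and third visit".

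On allocation, section 2.6 describes an external researcher "performing a simple randomization" for 40 patients, with no stratification factor.

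**The concern.** With one baseline and one follow-up value per outcome, there are two common ways to use the baseline: subtract it, or adjust for it. Subtraction fixes the baseline coefficient at 1, whereas adjustment estimates it. When the pre-post correlation is below 1 and the variances are similar at the two visits, subtraction has two consequences:

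- The change score carries baseline noise, so the treatment effect is estimated less precisely.
- If the arms differ at baseline by chance, the change score removes too much of that difference. In the trial at hand, the estimate is then shifted.

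Baseline p-values only describe an imbalance and leave the efficacy estimate unchanged. Letting a normality test choose the method also means that whether means or ranks are compared is settled only after the data are seen.

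At stake is precision in a trial of 40 people, where the information needed to improve it is already being collected.

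**Working it through.** **1. The article's own figure.** Section 2.8.1 gives a MAS difference of 0.75 ± 0.82, d = 0.93, and at least 38 participants for 85% power. On alpha it says only "An alpha level of 0.05 was assumed to perform the analysis", without sidedness. The printed figures give 0.75/0.82 = 0.915, close to 0.93. With d = 0.93 and 85% power, the required total is:

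- one-sided: 36 (t-test) or 38 (Mann-Whitney, relative efficiency 3/π);
- two-sided: 44 (t-test) or 46 (Mann-Whitney).

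So 38 is recovered only one-sided. The two-sided starting figure used below is therefore mine and not the article's.

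**2. Inputs for the illustration.** From the article: N = 40, alpha 0.05, d = 0.93 and d = 0.49 (the printed value for pressure pain). Assumed: a two-sided test, exactly 20 per arm, a continuous outcome, d in units of the SD of change, and r between 0.5 and 0.9.

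**3. Variance ratio.** With equal SD σ at both visits:

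- Var(change) = 2σ²(1 − r)
- Var(ANCOVA residual) = σ²(1 − r²)
- ratio = (1 − r²) / [2(1 − r)] = (1 + r)/2

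This is 0.75 at r = 0.5, 0.85 at r = 0.7 and 0.95 at r = 0.9. Estimating the baseline slope in a sample this small inflates the ANCOVA variance by about 1 + 1/37, giving 0.770, 0.873 and 0.976.

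**4. Power.** Change score: noncentrality = 0.93 / √(1/20 + 1/20) = 2.941, critical t with 38 df = 2.024, power 81.8%. For ANCOVA, divide 2.941 by the square root of the inflated ratio and use 37 df (critical t = 2.026).

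| r | Noncentrality (d = 0.93) | ANCOVA power, d = 0.93 (change score 81.8%) | ANCOVA power, d = 0.49 (change score 32.7%) |
|---|---|---|---|
| 0.5 | 3.351 | 90.4% | 40.5% |
| 0.7 | 3.148 | 86.5% | 36.5% |
| 0.8 | 3.059 | 84.6% | 34.8% |
| 0.9 | 2.977 | 82.6% | 33.3% |

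At r = 0.95 the inflated ratio is 0.975 × (1 + 1/37) = 1.001, so the gain has gone.

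**5. If the SD is of post-treatment scores.** The article does not say which SD 0.82 is. On this reading, change-score power is 81.8% at r = 0.5 and 95.9% at r = 0.7, against 90.4% and 97.7% for ANCOVA.

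**6. Baseline imbalance.** With 20 per arm, the baseline mean difference has SD √(1/20 + 1/20) = 0.316 in outcome SDs. The chance of a difference of at least 0.3 SD in either direction is 2[1 − Φ(0.3/0.316)] = 0.34 for any one outcome. Given such a difference, the change score subtracts 0.3 SD where regression predicts a carry-over of 0.3r. The conditional shift is therefore 0.3(1 − r): 0.15 SD at r = 0.5 and 0.03 SD at r = 0.9.

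**The case against.** The strongest reply is that the planned analysis is valid. Over repeated randomisations the change-score comparison is unbiased, and a 34% chance of a 0.3 SD imbalance is ordinary randomness. This stands: the shift in step 6 is conditional on the imbalance that happens to occur, and the point is about efficiency.

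A reader might infer that adjustment would raise MAS power from 82% to 87–90% at no cost. The article does not support that. It claims 85%, not 82%, and gives no sidedness, no r and no description of the SD. The upper figures need r of about 0.5 to 0.7. The MAS is also a coarse ordinal scale: section 2.8.2 lets the nature of the variable guide the test, so Mann-Whitney is the likely choice (79.9% two-sided under the 3/π approximation), and the model proposed below for the MAS is not linear ANCOVA. No power has been computed for it. Nor can one say that every confidence interval would narrow, since retest correlations for gait, range of movement and electromyography are not given.

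A reader might also infer that the Kolmogorov-Smirnov step switches methods largely by chance and harms the error rate. Neither is shown. In simulation, the Lilliefors form at n = 20 detected a lognormal with sigma 0.5 in about 34% of samples, but at n = 40 in 62%, and the article does not say whether the check is per arm or pooled. For an assumed discrete MAS change distribution it rejected in 99% of samples, so ranks would nearly always be chosen. Running the whole two-step procedure on differences of correlated lognormals (sigma 0.5, r = 0.6, 20 per arm, 4,000 runs) gave a type I error of 4.9%. What remains is that the comparison, means or ranks, is left to the data.

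**Conclusion.** The point holds as an efficiency weakness in a valid analysis. Section 2.8.2 states the method, so this is not a detail left to an unseen analysis plan.

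On the stated assumptions, the gain at d = 0.93 runs from about 9 percentage points at r = 0.5 to about 1 point at r = 0.9. At d = 0.49 it runs from about 8 points to less than 1, and adjustment does not rescue power for an effect of that size. These figures illustrate a continuous outcome and are not a forecast for the MAS. The direction does not depend on which SD was meant, as long as r stays below about 0.95.

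The two-sided shortfall against the stated 85% is a separate sample-size matter, and this conclusion does not rest on it.

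**What to change.** Replace the between-group sentence in section 2.8.2 with:

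> Each continuous outcome at the third visit will be compared between arms by ANCOVA with treatment and the baseline value of that outcome (adjusted mean difference, 95% CI). MAS will be compared by a proportional-odds model adjusted for baseline MAS.

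Fix these methods before unblinding, do not let the Kolmogorov-Smirnov test select the method for efficacy outcomes, and present baseline data descriptively without significance tests.

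The cost is one degree of freedom per model and, for the MAS, the proportional-odds assumption. No extra patients, visits or measurements are needed.
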